#### 2.2.2. Statistical Analysis

***Data analysis*.** We will present as means and standard deviations the descriptive statistics on cognitive and biological markers in the three treatment groups. The association between categorical variables will be analyzed using the Chi-square test.

The Automatic Linear Modeling (ALM) model that is based on a machine learning approach to find the best predictive model using available data will be used. A set of neuropsychological/biological values will be analyzed as independent input variables, while the scores of IFI or SHARE-FIt scales will be analyzed as continuous output (target) (dependent) variables. Longitudinal comparisons will be performed using univariate analysis, where the clinical parameters relating to the IFI and SHARE-FIt scales will be entered as dependent variables, the significant values obtained from ALM as covariates, and time and treatment as fixed factors. For the metabolomic analysis, PCA analysis (Principal Component Analysis) and a univariate analysis will be performed to evaluate the effects of the treatment on the presence/distribution of the metabolites. 

With the aim to correlate any clinical/cognitive improvements with molecular profiles to identify markers associated with response to treatment, the generalized linear mixed model (GLMM) will be used where the biological values and those relating to neuropsychological tests and the times of follow-up will be analyzed as independent input variables, while the values relating to the IFI or SHARE-FIt scales will be analyzed as weight variables and the treatments as (dependent) variables. “Air treatment” will be used as a comparison variable. All these analyses will be performed using SPSS ver. 29.

Differentially expressed genes will be identified using R-Bioconductor by applying both a fold change and p-value threshold (R-Limma test *p* value < 0.05; |Log2 fold-change ratio| > 1.0). By Fisher’s exact test, we will analyze the categories and functional pathways of upregulated or downregulated genes, using all genes in the array as the “reference” genome, or through the use of Ingenuity Pathway Analysis (IPA, Qiagen, Venlo, The Netherlands) to infer alterations in biological pathways and functions. 

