## Abstract

Cognitive frailty (CF) is a heterogeneous syndrome that is becoming one of the most serious health problems as the world’s population age is increasing. Elucidating its biological mechanisms as well as prevention and treatments is becoming increasingly significant, particularly in view of the associated health costs. We presented the study protocol of a research project funded by the Italian Ministry of Health (grant number RF-2016-02363298) aiming to investigate the cognitive and neuropsychological effects of a 5-week treatment with therapy based on the regenerative properties of ozone (O_3_) in a cohort of subjects stratified according to CF scores. We also studied the potential effects of O_3_ on blood-based biomarkers indicative of specific biological systems that may be altered in CF. Seventy-five older persons were recruited and randomly assigned to receive the active treatment (150 cc of oxygen-O_2_-O_3_ mixture at the concentration of 30 µg of O_3_ per cc of O_2_), O_2_, or the placebo (air) for 5 weeks. The main endpoints were the change in the scores of clinical scales from baseline (T0) to weeks 3 (T3), 9 (T9), and 15 (T15) after treatment and the change in biomarker levels resulting from transcriptomics, proteomics, and metabolomic patterns at the same times. The positive results from this study could have important clinical implications.

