#### 2.1.12. Statistical Analysis

***Sample size*.** The power analysis was performed by the analysis of the univariate linear regression test. Using the accuracy of the model IFI scale as a multiple partial coefficient (R^2^) and the neuropsychological tests as fixed predictors, we found a power effect of 0.92 related to our population of 76 subjects. Similar findings (power effect of 0.80) were found when we considered the SHARE-Fit scale.

### 2.2. PART 2

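### The covariates of the IFI/SHARE-FIt treatment model are picked by a search on those same outcomes in the same 75 people, and the candidates are not limited to baseline values

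*Protocol article*

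**What the plan says.** Section 2.2.2 (Statistical Analysis, Data analysis) of the protocol article sets out two linked steps.

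- **Search.** ALM is introduced as a "machine learning approach to find the best predictive model using available data". Its inputs are described only in general terms: "A set of neuropsychological/biological values will be analyzed as independent input variables". The target is the IFI or SHARE-FIt score.
- **Treatment model.** The longitudinal comparison has IFI and SHARE-FIt as dependent variables and time and treatment as fixed factors. It takes "the significant values obtained from ALM as covariates".

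Section 2.1.7 makes change in IFI or SHARE-FIt at T3, T9 and T15 the primary endpoint. The Abstract gives the sample: "Seventy-five older persons were recruited and randomly assigned to receive the active treatment", O2 or placebo.

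Section 2.2.2 does not state how many inputs ALM receives, whether they are baseline or follow-up values, or what selection rule is used.

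**The concern.** The adjustment set of the primary comparison is not fixed in advance. It is whatever best fits the primary outcome in the trial's own data. Two things are at stake.

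1. **Chance covariates.** With 75 people and a few dozen candidates, some will fit the outcome by chance. ALM does not know about treatment. In the arm-by-arm data, a noise variable that happens to line up with treatment also lines up with the outcome when treatment works. The search favours such variables, and adjusting for them takes away part of the real effect.
2. **Post-treatment covariates.** Table 1 repeats the neuropsychological scales and blood sampling at T3, T9 and T15, and the treatment model has time as a factor. Nothing confines the ALM inputs to T0. The Introduction makes the effect of therapy on cognition and on blood biomarkers the aim of the trial, and the Discussion expects ozone to influence immune–inflammatory and oxidative-stress systems. Conditioning on follow-up values of these measures removes the part of the effect that runs through them.

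**Working it through.** The plan gives no figure of its own for this step, so there is none to reproduce. The check asks what the stated rule does in a trial of this size.

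**Number of candidates**

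| Source | Measures | Count |
|---|---|---|
| Section 2.1.9, tests at every visit | MMSE; RAVLT immediate and delayed; ROCF recall and copy; TMT-A and TMT-B; action naming and object naming; CPM47; FCSRT; FNAT | 12 |
| Section 2.1.9, further tests | digit span forward and backward; story recall; FPL; FPC; Token Test; sentence comprehension; ideomotor apraxia right and left | 9 |
| Section 2.1.9 | CRP | 1 |
| Section 3 (Discussion), named proteins | IL-1β, IL-6, TNFα, MCP-1, RANTES, MIP1, VEGF, BDNF, NGFβ | 9 |
| **Total** | | **31** |

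**Assumptions, since the article does not give them.** n = 75, three arms of 25, one observation per person, independent normal candidates with no true relation to the outcome. Forward selection uses one of two rules: enter while p < 0.05, or enter while AICc = n·ln(RSS/n) + 2K + 2K(K+1)/(n−K−1) falls, with K the number of parameters.

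**Chance of selecting at least one noise predictor**

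- *Rule p < 0.05:* 1 − 0.95^31 = 0.80. Simulation: about 80%.
- *Rule AICc:* for the first term K goes from 2 to 3, so the penalty rises by 2 + 24/71 − 12/72 = 2.17. The entry condition is F > 73·(e^(2.17/75) − 1) = 2.14 on 1 and 73 df, which corresponds to p of about 0.147. Then 1 − 0.853^31 = 0.99. Simulation: about 99%.
- Counting only terms with p < 0.05 in the final model, the simulated figures are 79% (p rule) and 91% (AICc).

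**Apparent fit.** Mean in-sample R² is 0.12 (p rule) and 0.23 (AICc). The true value is 0.

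**Effect on the treatment test.** The test compares residual sums of squares with and without treatment, adjusted for the selected covariates. An effect of 0.8 SD in one arm is assumed.

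| Quantity | No selected covariates | With covariates selected from 31 noise candidates |
|---|---|---|
| Power | about 81–82% | about 68–77% |
| Type I error | near 5% | near 5% |

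Across the simulations run for this point, type I error with selected baseline noise covariates lay between 0.043 and 0.063. The mechanism shows in the estimate: with a true effect of 0.80 SD, the mean adjusted estimate was 0.76 with 20 noise candidates and 0.69 with 50. Thirty-one lies between these counts.

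**Effect of a follow-up covariate.** If treatment shifts the covariate by 0.8 SD and the covariate's slope on the outcome is b, the adjusted effect is 0.80 − 0.8·b.

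- b = 0.3: 0.80 − 0.24 = 0.56. Simulated power 48% against 82% unadjusted.
- b = 0.6: 0.80 − 0.48 = 0.32. Simulated power 24% against 81% unadjusted.

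The slopes and the shift are assumptions. The direction does not depend on them as long as treatment improves the covariate and the covariate is positively related to improvement in the outcome.

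**The case against.** The best defence is that this is a condensed article about a self-described pilot trial, which says its results need confirmation in a larger population. Adjusting for real predictors of frailty gains precision, and some of the cognitive tests may be real predictors. The simulation assumes that none is, that candidates are uncorrelated and that a particular selection rule applies; ALM as run may differ. All of this limits the exact figures. It does not rescue the rule, because a list of baseline covariates set in advance brings the same gain in precision without the search. Confirmation in a later, larger study does not repair this trial's own primary comparison.

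A reader might infer several stronger points that the documents do not support.

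- **That whole omics matrices are searched.** Section 2.2.2 says neuropsychological/biological values. In the same section metabolites go to PCA and univariate analysis, and genes to limma.
- **That most selected predictors would be noise.** This depends on the candidate count. With five real predictors assumed (total R² 0.25), the noise share is 34–44% at 30 candidates and passes half only at about 50 (54–65%).
- **That treatment p-values become invalid.** With baseline noise covariates, type I error stayed near 5%. The harm is lost power and a shrunken estimate.
- **That the lack of a hold-out or resampling step is an error.** The article is silent, and such detail may stand in a fuller document.
- **That ALM accuracy produced the stated power.** Section 2.1.12 refers to model accuracy ("Using the accuracy of the model IFI scale as a multiple partial coefficient") with "the neuropsychological tests as fixed predictors", but does not name ALM or a selection step. The link is possible, not shown.

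**Conclusion.** The point stands in a limited form. Section 2.2.2 states a rule under which the primary outcome selects its own adjustment covariates in the same 75 people, from a candidate set that is open in number and timing. Further detail elsewhere could narrow the candidates, but as long as the rule stands the covariates remain outcome-driven.

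With the roughly 31 measures that the article names, all taken as noise, the search selects at least one in about 80–99% of runs, and power for a 0.8 SD effect drops by between about 4 points (81 to 77) and 14 points (82 to 68). These figures rest on independent candidates, forward selection and one observation per person. Correlated tests, repeated visits or real predictors would change them, and real predictors could offset the loss. The larger risk is timing: if follow-up values are used, the estimated treatment effect is biased towards zero by an amount that the article gives no means to bound.

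**What to change.** In section 2.2.2, replace "the significant values obtained from ALM as covariates" with a short list of covariates fixed before analysis and taken from baseline only. An example is the baseline value of the scale being analysed, the cognitive frailty tertile used to balance allocation, age and sex. State that no value measured after the start of treatment enters the model as a covariate.

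Keep ALM as a separate exploratory analysis of which measures go with IFI and SHARE-FIt. Repeat the whole selection inside a resampling scheme such as cross-validation, report its accuracy out of sample, and do not carry its selections into the treatment model.

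The cost is slightly more analysis work and a lower reported ALM accuracy. No new data are needed. The Discussion describes the molecular analyses as still ongoing; the list should be fixed before the treatment comparison is run.

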#### 2.1.4. Study Schedule

In Figure 1, the study schedule of the following trial protocol is shown.

Participants were invited to undergo a face-to-face clinical assessment and neurocognitive batteries. In addition, subjects were asked about their socio-demographic status, their lifestyle, and their diet habits. Body Mass Index (BMI) was calculated too. The Everyday Memory Questionnaire (EMQ) was administrated to evaluate the presence of Subjective Memory Complaints (SMCs), whereas the Cognitive Reserve Index questionnaire (CRI-q) was used to measure cognitive reserve. Symptoms of depression were evaluated with the Geriatric Depression Scale (GDS), whereas physical health in general was estimated by the number of chronic diseases, by the Cumulative Illness Rating Scale (CIRS index), and by the number of drugs. Moreover, functioning skills in daily life were valued through the Barthel Index for Activities of Daily Living (Barthel index), Tinetti, and Instrumental Activities of Daily living (IADL) scales, in order to investigate the functional impact of any cognitive difficulties. Finally, an assessment of physical activity in daily life was performed. 

Specific scales/tools were used to assess the frailty status: the “Italian Frailty Index” (IFI) [31], an Italian version of the frailty index based on the accumulation of age-related deficits; the Frailty Instrument (FIt) for primary care based on the Survey of Health, Aging and Retirement in Europe (SHARE-FIt) [32], valuating five items (i.e., grip strength and four self-reported items: fatigue, loss of appetite and/or eating less than usual, difficulties climbing stairs and/or walking 100 m, and low level of physical activity); and the CDR scale to quantify the severity of symptoms of dementia.

A baseline neuropsychological visit, scheduled within a mean of 20 days of the face-to-face clinical assessment, was administered to all eligible participants, who were then allocated to one of the three intervention groups. A blood sample was collected for biomarker measurement from all subjects. Follow-up neuropsychological visits included (i) a visit 3 months after treatment (T3); (ii) a midpoint visit 9 months after treatment (T9); and (iii) an endpoint visit 15 months after treatment (T15). In each follow up, we collected blood samples for biomarker measurement.

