#### 2.1.7. Primary and Secondary Endpoints

The primary endpoint was the change in the scores of the clinical IFI or SHARE-Fit scales from baseline to the T3, T9, and T15 trial period after treatment.

The secondary endpoint was the change in the molecular levels (RNA and proteins) from baseline over the T3, T9, and T15 trial period after treatment.

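### The longitudinal treatment comparison on IFI and SHARE-FIt names no term for repeated visits by the same person, so its treatment test is miscalibrated

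*Protocol article*

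**What the plan says.** The primary endpoint (section 2.1.7) is the "change in the scores of the clinical IFI or SHARE-Fit scales from baseline to the T3, T9, and T15 trial period after treatment". The Abstract gives the size, "Seventy-five older persons were recruited and randomly assigned to receive the active treatment", O2 or air, and section 2.1.4 confirms three intervention groups.

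The treatment comparison on those scales is in section 2.2.2: "Longitudinal comparisons will be performed using univariate analysis", in which "the clinical parameters relating to the IFI and SHARE-FIt scales will be entered as dependent variables", together with "the significant values obtained from ALM as covariates, and time and treatment as fixed factors". SPSS 29 is the software. No subject factor, random effect, repeated-measures structure or derived change score is mentioned.

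The only mixed model in the article is in the next paragraph of the same section and serves another aim, finding markers of response. In it, "the values relating to the IFI or SHARE-FIt scales will be analyzed as weight variables and the treatments as (dependent) variables". It does not test treatment against frailty score.

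**The concern.** With time as a factor, each participant supplies several rows. Rows from one person are normally positively correlated, and treatment varies only between people. A model with a single pooled residual takes its error for the treatment comparison from all rows as if each were a new person. The standard error of the treatment main effect is then too small, and chance differences between arms are declared significant too often.

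A treatment-by-time term tested against the same pooled error goes wrong in the opposite direction. That contrast is within-person, but the pooled error also contains the variation between people, so a real effect is likely to be missed.

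This is the only described analysis that compares the arms on the primary scales, so the trial's main clinical conclusion rests on it.

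**Working it through.** **Inputs from the article.** 75 people (Abstract, section 2); three arms (section 2.1.4); scores at baseline, T3, T9 and T15 (section 2.1.7), so four score rows per person, or three if only follow-up visits are modelled; model terms as listed in section 2.2.2.

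**Inputs assumed, because the article does not give them.** 25 per arm; a two-sided 5% level (0.05 appears only for gene expression); equal correlation ρ between any two visits of one person (compound symmetry); no covariates.

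**The plan's own figure.** Section 2.1.12 states power of 0.92 (IFI) and 0.80 (SHARE-FIt) with 76 subjects. That calculation regresses the scales on neuropsychological tests, not on treatment, and gives neither R² nor the number of predictors. At N = 76, power of 0.92 would need R² = 0.133 with one predictor, 0.20 with five or 0.32 with twenty. The figure can be neither confirmed nor refuted, and it does not bear on this comparison.

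**Formula.** With T rows per person, the variance of an arm mean is inflated by the design effect DE = 1 + (T − 1)ρ. To a close approximation the false-positive rate is P(F(2, 72) > Fcrit / DE), where 72 = 75 − 3 is the correct between-person df and Fcrit is the 5% point the naive model uses:
- four rows: 300 − 6 = 294 residual df, Fcrit = 3.026;
- three rows: 225 − 5 = 220 residual df, Fcrit = 3.037.

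**Change scores.** Under compound symmetry with variance σ², a change from baseline has variance 2σ²(1 − ρ), and two changes sharing that baseline have covariance σ²(1 − ρ). Their correlation is 0.5 whatever ρ is, so with three changes DE = 1 + 2 × 0.5 = 2.

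| Rows per person | ρ | DE | Fcrit / DE | Formula | Simulation |
|---|---|---|---|---|---|
| 4 scores | 0.1 | 1.3 | 2.328 | 10% | 10% |
| 4 scores | 0.2 | 1.6 | 1.892 | 16% | about 15% |
| 4 scores | 0.5 | 2.5 | 1.211 | 30% | 30–31% |
| 4 scores | 0.7 | 3.1 | 0.976 | 38% | 38% |
| 4 scores | 0.9 | 3.7 | 0.818 | 45% | 44–46% |
| 3 scores | 0.5 | 2.0 | 1.518 | 23% | 22–23% |
| 3 scores | 0.7 | 2.4 | 1.265 | 29% | 29% |
| 3 scores | 0.9 | 2.8 | 1.085 | 34% | 35% |
| 3 changes | any | 2.0 | 1.518 | 23% | 22–23% |

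The simulations used 20,000 null trials per setting. At ρ = 0 the naive test is calibrated (about 5%).

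**Treatment-by-time on four score rows, if fitted with the same pooled error.** Under the null it rejects about 0.04% at ρ = 0.5 and essentially never at 0.7. For a 0.5 SD shift in one arm at all follow-ups and ρ = 0.7, power is about 0.6%, against about 65% with the within-person error.

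**After adding a subject term** (four rows, compound symmetry), the main effect and the interaction both return to about 5%. If the true correlation is instead first-order autoregressive at 0.7 or 0.9, the main effect stays at about 5%, but a simple subject term leaves the interaction at 6.9–7.6%. The covariance structure therefore also has to be stated.

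**The case against.** The best defence is that a journal article condenses the plan and the subject term was simply left out. That would carry weight if the text said only that scores would be compared over time. Instead it gives every variable a role (dependent, covariate, fixed factor), calls the analysis univariate, and reserves its mixed model for a different question. Followed as written, the model is wrong for repeated data.

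Other parts of the defence stand and limit the claim:

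- **Score or change.** A reader might infer that the model tests score level with baseline included: 300 independent rows and a constant effect diluted to three quarters. The article does not say so. Section 2.1.7 points to change, and change scores have no baseline row and no such dilution. The error is then about 22–23%.
- **Number of measurements.** Table 1 ticks clinical scales at baseline only, and section 2.1.4 calls the follow-ups neuropsychological visits. Four IFI and SHARE-FIt scores per person follow from section 2.1.7 but are not secure.
- **Interaction.** A reader might infer that no treatment-by-time term will be fitted. The article names the factors and is silent on their interaction, a detail commonly left to the analysis plan. The interaction result is therefore conditional.
- **Covariates.** The calculations omit the covariates from the modelling step. Those that explain differences between people lower the residual correlation and the inflation, but remove it only if that correlation reaches zero.
- **Pilot status.** The Discussion calls the trial a pilot and wants confirmation in a larger population. That tempers the conclusions; it does not make the test valid.

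**Conclusion.** The point holds. The listed model has no term for repeated measurement, and the treatment main-effect test is too liberal on each reading of the dependent variable examined: about 30–44% false positives with four score rows and 22–35% with three (correlation 0.5–0.9), about 22–23% with three change scores, and about 10–15% with four rows at a residual correlation of only 0.1–0.2.

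These sizes rest on equal arms, a 5% level, compound symmetry and no covariates, none of which the article states. The direction rests only on a positive residual correlation within persons. No single figure should be quoted as the plan's error rate, because the article settles neither the dependent variable nor the number of measurements. Since this is the treatment comparison on the primary scales, it should be corrected before the analysis is run.

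**What to change.** Replace the univariate model, for each scale, with a linear mixed model for repeated measures (SPSS MIXED):

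- dependent variable: change from baseline at T3, T9 and T15;
- fixed effects: treatment, visit, treatment-by-visit and baseline score;
- a stated within-person covariance, for example unstructured, with a named fallback if it does not converge;
- reported result: the O2-O3 minus air contrast with its 95% confidence interval.

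State explicitly that change from baseline is what is modelled, and reconcile the clinical-scales row of Table 1 with section 2.1.7, so that the visits at which IFI and SHARE-FIt are measured are clear.

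The cost is revised wording and a different procedure in the software already planned. The model change itself needs no new data, and the article lists this analysis among the steps still to be done. Confidence intervals for the treatment main effect will be wider, but valid.

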Since 1840, from its discovery, ozone (O_3_) and, consequently, oxygen (O_2_)-O_3_ therapy has expanded into the medical field, giving rise to compelling research in the recent decades which validates its clinical value [21]. Several papers [22,23,24] emphasized its relevant medical features, such as virucidal and bactericidal effects, inflammatory modulation, and circulatory stimulation, with considerable applications in several medical fields [25]. O_3_ is considered one of the most powerful oxidizing molecules in nature [26]. Indeed, its function is strictly associated with its power to directly interact with lipoproteins, phospholipids, viral capsids, and bacteria envelopes. Particular attention was recently paid to further specific O_3_ activities related to the cellular and humoral immune system which contribute to the proliferation of immunocompetent cells and the synthesis of immunoglobulins as well as biologically active substances (interleukins, leukotrienes, and prostaglandins). In this sense, O_3_ also seems to activate macrophage function and increase the sensitivity of microorganisms to phagocytosis. Finally, it has also been reported that O_3_ can interact with blood cells or other elements of the circulatory system, which would have beneficial properties to O_2_ metabolism, the antioxidant defense system, cellular energy, and microcirculation [26].

If, on the one hand, experimental evidence provides a solid preclinical rationale for the application of O_2_-O_3_ therapy to improve cognitive profiles in aging [27,28,29,30], clinical studies supporting its potential beneficial effects on cognition in humans are not available.

Here, we presented the study protocol of a research project funded by the Italian Ministry of Health (grant number RF-2016-02363298). The main aims of this research project are (1) to clarify the potential cognitive and neuropsychological effects of a 5-week treatment with O_2_-O_3_ therapy on older adults with frailty; (2) to elucidate the potential effects of this therapy on blood-based biomarkers associated with transcriptomics, proteomics, and metabolomics patterns. We describe the protocol study by dividing the Material and Methods section into two parts, where we specify what steps have been performed (PART 1) and what steps will need to be performed (PART 2). 

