#### 2.1.9. Data Collection

***Neuropsychological batteries*.** All participants were tested at each visit with the Mini Mental State Examination (MMSE) [33] to assess the global cognition, and several cognitive tests were selected to assess a broad range of cognitive abilities: RAVLT, immediate and delayed recall, ROCF Recall, TMT-A, TMT-B, ROCF copy, action and object naming subtests from the Battery for the Assessment of Aphasic Disorders (B.A.D.A), Raven’s Colored Progressive Matrices (CPM47), the Free and Clued Selective Reminding Test (FCSRT), and the Face–Name Association task (FNAT) [34]. In addition, baseline assessment (time = T0) included the administration of a digit span forward and digit span backward test. Story recall, phonemic verbal fluency (FPL) and semantic verbal fluency (FPC) tasks, the Token Test Auditory sentence comprehension subtest from BADA, and the De Renzi ideomotor apraxia test (right and left upper limb) were also used [35]. 

***Biological measures*.** Fasting venous blood samples were collected in the morning at the baseline (T0) and at follow-ups T3, T9, and T15 for the evaluation of alterations/modulations at the molecular level before and after treatment. 

**Proteomic analyses.** We used anticoagulant-free tubes and EDTA tubes to collect serum and plasma samples, respectively. Serum tubes were kept at room temperature for 1 h followed by 1 h at 4 °C before serum separation by centrifugation (2000× *g* for 10 min). Plasma tubes were immediately centrifuged at 2000× *g* for 10 min. Both serum and plasma samples were stored at −80 °C until the time of the assay. 

An assay was also performed for C-reactive protein (CRP) on serum samples from each subject at time T0.

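### The treatment model for IFI/SHARE-FIt adjusts for data-selected neuropsychological and biological values not restricted to baseline; separately, no model has a cognitive score as outcome although cognition is aim 1

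*Protocol article*

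**What the plan says.** **The treatment model.** Section 2.2.2 (Data analysis) describes two linked steps. In the first, ALM predicts IFI or SHARE-FIt: "A set of neuropsychological/biological values will be analyzed as independent input variables". In the second, the longitudinal comparison, "the clinical parameters relating to the IFI and SHARE-FIt scales will be entered as dependent variables", with "the significant values obtained from ALM as covariates, and time and treatment as fixed factors". This is the only model the article gives for comparing treatments on the primary endpoint (section 2.1.7). Neither step says which visit the candidate values come from.

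**What treatment is expected to change.** The Introduction gives two aims: "to clarify the potential cognitive and neuropsychological effects of a 5-week treatment with O_2_-O_3_ therapy on older adults with frailty", and "to elucidate the potential effects of this therapy on blood-based biomarkers associated with transcriptomics, proteomics, and metabolomics patterns". The Discussion likewise expects treatment to modulate gene expression and to benefit cognition.

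**When these variables are measured.** Section 2.1.9 says "All participants were tested at each visit with the Mini Mental State Examination", along with further tests, and that blood is drawn "at the baseline (T0) and at follow-ups T3, T9, and T15 for the evaluation of alterations/modulations at the molecular level before and after treatment". Table 1 shows neuropsychological scales and blood samples at baseline, T3, T9 and T15.

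**Where cognition is analysed.** The endpoints in section 2.1.7 are frailty scales (primary) and molecular levels (secondary). In section 2.2.2, cognitive scores appear as group means and SDs, as ALM inputs, as possible covariates, and as inputs to a GLMM whose dependent variable is treatment.

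**The concern.** There are two distinct problems.

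**Covariates.** Randomisation protects a comparison adjusted for variables measured before treatment. It does not protect one adjusted for variables that treatment may have changed. By the trial's own hypothesis, the candidate covariates at T3, T9 and T15 are mediators or outcomes. Adjusting for them replaces the total effect of treatment on frailty with whatever does not pass through the selected variables. Where a covariate and frailty share a cause, it can also produce a difference that treatment did not cause. Selecting the covariates by their fit to the outcome in the same data adds a further distortion, even for baseline values.

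**Cognitive aim.** No model estimates a treatment effect on a cognitive score. The first aim could therefore be reported only descriptively, or through a model that predicts treatment from test scores.

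**Working it through.** **The plan's own power figure.** Section 2.1.12 states power of 0.92 for IFI with 76 subjects and 0.80 for SHARE-FIt, with neuropsychological tests as predictors. It cannot be reproduced, because R², the number of predictors k and alpha are not given. Assuming alpha 0.05 and the overall F test (noncentrality N·R²/(1−R²), df k and N−k−1, N = 76), these values of R² would be needed:

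| k | R² for power 0.92 | R² for power 0.80 |
|---|---|---|
| 1 | 0.13 | 0.10 |
| 5 | 0.20 | 0.15 |
| 10 | 0.25 | 0.20 |
| 20 | 0.32 | 0.26 |

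Whatever the inputs, this is the power to detect an association between tests and frailty. It says nothing about the power of the adjusted treatment comparison.

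**Inputs for the illustrations.** From the documents: 75 people and three arms. Assumed: 25 per arm (75/3), total effect 0.8 SD, two-sided alpha 0.05, and the mediation shares, slopes and candidate pools below. A 25 v 25 contrast has about 80% power at 0.8 SD, since (1.96 + 0.84)·√(2/25) = 0.79.

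**1. Follow-up covariate that carries part of the effect.** Adjusted effect = total × (1 − share mediated). At 50%, 0.8 × 0.5 = 0.40 SD; at 75%, 0.8 × 0.25 = 0.20 SD. Simulation (4,000 runs; covariate-outcome slope 0.6; baseline/follow-up correlation 0.7):

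| Share mediated | Unadjusted: effect, power | T0 value: effect, power | Follow-up value: effect, power |
|---|---|---|---|
| 0% | 0.80, 0.79 | 0.80, 0.86 | 0.80, 0.93 |
| 25% | 0.80, 0.79 | 0.80, 0.85 | 0.60, 0.72 |
| 50% | 0.81, 0.79 | 0.81, 0.86 | 0.40, 0.38 |
| 75% | 0.80, 0.79 | 0.80, 0.86 | 0.20, 0.12 |
| 100% | 0.80, 0.79 | 0.80, 0.85 | 0.00, 0.05 |

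The estimate depends only on the share mediated. Power also depends on the assumed slope: other simulations at 50% mediation gave 0.31 and 0.32, hence the range of about 0.3 to 0.4.

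**2. Follow-up covariate that shares a cause with frailty, with no effect on frailty.** Suppose treatment shifts the marker by 0.8 SD and an unmeasured cause explains 50% of the variance of each variable. The within-arm slope of frailty on the marker is then 0.5, and the adjusted effect is 0 − 0.5 × 0.8 = −0.40 SD. Simulation gives −0.40 SD with rejection of 0.30 to 0.32, against about 0.05 unadjusted.

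**3. Baseline covariates chosen by fit to the outcome.** The setting is n = 75, three arms, pure-noise candidates, and the five that best fit the outcome kept without regard to arm. A true 0.80 SD becomes about 0.72 to 0.74 SD with 20 candidates and about 0.52 SD with 1,000. The five best of 1,000 noise markers explain about 42% of the outcome variance. When treatment moves the outcome, covariates that fit the outcome by chance also tend to be unbalanced between arms, and so absorb part of the effect. With no treatment effect, rejection stayed near 5% (5.6% in 1,500 runs).

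**4. Models for cognition.** Taking the analyses of section 2.2.2 in turn: the longitudinal model has IFI/SHARE-FIt as dependent variable; the GLMM has treatment as dependent variable, test scores as inputs and frailty scores as weights; the metabolite and gene analyses concern molecular data. None has a cognitive score as outcome.

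**The case against.** **The time point is open.** A reader might infer that the plan does use follow-up values and so certainly adjusts the effect away. The text does not say so. Section 2.1.12 relates IFI to the tests with no time or treatment term, which would fit a baseline reading. With T0 values, mechanisms 1 and 2 disappear. This stands, and the bias must be stated conditionally. A model with time as a factor and covariates measured at every visit makes follow-up values an equally natural reading, however, and the selection effect in step 3 applies to T0 values too.

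**The article is a summary.** A fuller protocol or SAP might restrict the covariates or name cognitive outcome models, so the absence can be asserted only of the article. The covariate rule itself is stated there, and it permits a harmful reading.

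**Cognition is not unanalysed.** A reader might conclude that the cognitive scores get no analysis at all. That is too strong: means and SDs by group are planned, and the GLMM relates test scores to treatment with air as comparator. With the roles reversed, though, it does not estimate a treatment effect on cognition. The biological aim does have its own tests.

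**The two problems are not cause and effect.** The missing cognitive model might be read as a result of the ALM step. It is a separate mismatch between aim 1 and the endpoints of section 2.1.7. Removing the ALM covariates would not cure it.

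**The sizes are illustrative.** The 0.8 SD effect, the mediation shares, the shared-cause variance and the candidate pools are not in the documents. Nor does selection of noise covariates by itself inflate the type I error.

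**Conclusion.** The point holds in conditional form. The only treatment model given for the primary endpoint takes covariates selected for their fit to that endpoint, from variables the trial expects treatment to change, with no restriction to T0.

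- If follow-up values enter, the estimate loses the mediated share: 0.80 to 0.40 SD at 50%, with power of about 0.3 to 0.4 instead of 0.80. In the shared-cause case it shows a false −0.40 SD with about 30% rejection.
- If only T0 values enter, those errors vanish, but selection in the same 75 people still shrinks 0.80 SD to about 0.74 with 20 noise candidates and 0.52 with 1,000.
- Separately, aim 1 has descriptives and a role-reversed GLMM, but no model with a cognitive score as dependent variable.

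The direction of each effect follows from the design. The sizes rest on the assumed inputs. Pilot status does not remove the problem, because an estimate meant to guide a larger trial should be the randomised effect.

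**What to change.** 1. In section 2.2.2, allow only prespecified T0 covariates in the IFI/SHARE-FIt treatment model: the baseline value of the outcome, the CF tertile used for balancing, and a short list fixed now (age, for example).
2. Keep ALM as a separate exploratory prediction analysis whose results do not feed the treatment model.
3. For aim 1, add a longitudinal mixed model with neuropsychological score(s) repeated at every visit as outcome, and treatment, visit and treatment × visit as factors. The plan has no such model to reuse: its longitudinal comparison is described as univariate, and its one mixed model has treatment as the dependent variable. Section 2.1.9 lists 12 scores, from eight instruments, given at each visit. Name the score(s) in advance; a prespecified composite is one option.

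Section 2.2.2 belongs to the part of the article describing steps still to be performed. The cost is revised wording and one extra model on data already collected. The change should be recorded before treatment assignments are unblinded for analysis.
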